#### 4.3 TREATMENT COMPLIANCE

The subjects will be asked to bring the container of the study medication on the next follow-up visit and compliance for dosing will be assessed by examination of the container and tablet count by study personnel out of the sight of the subject.

|                                                         |                                                 |                                                           |
|---------------------------------------------------------|-------------------------------------------------|-----------------------------------------------------------|
| Prepared by:
[name]
Date: 22.06.2010 | Approved by:
[name]
Date:22.06.2010 | Protocol No. ZYH1.09.003.01 .PROT
Version No.: 1.0 (R) |
|---------------------------------------------------------|-------------------------------------------------|-----------------------------------------------------------|

|                                                                                  |                                                                                           |              |
|----------------------------------------------------------------------------------|-------------------------------------------------------------------------------------------|--------------|
| [figure not shown] | Clinical trial Protocol for ZYH1 – Phase II
ZYH1.09.003.01.PROT

DCGI Submission | Confidential |
|----------------------------------------------------------------------------------|-------------------------------------------------------------------------------------------|--------------|

## 5. OBSERVATIONS

### 5.1 EFFICACY

#### 5.1.1 Primary endpoint(s)

Percent change in TG levels from baseline to Week 6 and Week 12

#### 5.1.2 Secondary endpoint(s)

Percent change in following parameters from baseline to Week 6 and Week 12.

- LDL
- VLDL
- HDL
- Total cholesterol
- Non HDL Cholesterol (Measured value)
- Apo (a)
- Apo B
- Fasting insulin and C-peptide for HOMA beta & IR

### 5.2 SAFETY

Following parameters will be assessed

- General and Systemic Clinical Examination: cardiovascular system (CVS), respiratory system (RS), gastrointestinal system (GI), central nervous system (CNS) etc.
- Laboratory Investigations: Complete blood count (CBC), aspartate transaminase (AST), alanine transaminase (ALT), alkaline phosphatase (ALP), total bilirubin, γ- glutamyl transpeptidase (GGT), Serum proteins, Blood urea nitrogen (BUN), Serum creatinine and Creatinine phosphokinase (CPK)
- Frequency and severity of adverse events (AEs) for all subjects enrolled will be recorded.

|                                                         |                                                 |                                                           |
|---------------------------------------------------------|-------------------------------------------------|-----------------------------------------------------------|
| Prepared by:
[name]
Date: 22.06.2010 | Approved by:
[name]
Date:22.06.2010 | Protocol No. ZYH1.09.003.01 .PROT
Version No.: 1.0 (R) |
|---------------------------------------------------------|-------------------------------------------------|-----------------------------------------------------------|

|                                                                                  |                                                                                           |              |
|----------------------------------------------------------------------------------|-------------------------------------------------------------------------------------------|--------------|
| [figure not shown] | Clinical trial Protocol for ZYH1 – Phase II
ZYH1.09.003.01.PROT

DCGI Submission | Confidential |
|----------------------------------------------------------------------------------|-------------------------------------------------------------------------------------------|--------------|

- All AEs, will be classified using
  - causality
  - severity
  - seriousness

|                                                         |                                                 |                                                           |
|---------------------------------------------------------|-------------------------------------------------|-----------------------------------------------------------|

## 6. INVESTIGATIONAL PLAN

### 6.1 STUDY DESIGN AND PLAN

A prospective, multi-centric, open-label, single arm study to evaluate the safety and efficacy of 4mg of ZYH1 in hypertriglyceridemia in HIV associated lipodystrophy.

### 6.2 STUDY PROCEDURES AT EACH VISIT

All the subjects will be evaluated as per the Inclusion & Exclusion Criteria and will undergo a thorough general and systemic examination and appropriate laboratory investigations to rule out other concomitant diseases prior to enrolment into the study and initiation of therapy.

### 6.3 STUDY SCHEDULES

Study schedule for the trial is given in Table 1.

#### Details of visit schedule:

Informed consent will be obtained before any trial related activity.

#### 1) Visit 1, Screening/Enrolment Visit [Week $\geq$ -1 to 0]

- Subjects will be screened for the inclusion and exclusion criteria and those qualifying will be invited to participate in the study.
- Clinical evaluation will be done for baseline characteristics and anthropometry.
- After Clinical evaluations all baseline safety and efficacy parameters will be recorded as per Table 1.
- All laboratory investigations will be carried out after an overnight fasting.
- Enrolled Subjects will receive a study medication for next two weeks

|                                                         |                                                 |                                                           |
|---------------------------------------------------------|-------------------------------------------------|-----------------------------------------------------------|
| Prepared by:
[name]
Date: 22.06.2010 | Approved by:
[name]
Date:22.06.2010 | Protocol No. ZYH1.09.003.01 .PROT
Version No.: 1.0 (R) |
|---------------------------------------------------------|-------------------------------------------------|-----------------------------------------------------------|

|                                                                                  |                                                                                           |              |
|----------------------------------------------------------------------------------|-------------------------------------------------------------------------------------------|--------------|
| [figure not shown] | Clinical trial Protocol for ZYH1 – Phase II
ZYH1.09.003.01.PROT

DCGI Submission | Confidential |
|----------------------------------------------------------------------------------|-------------------------------------------------------------------------------------------|--------------|

## 2) Visit 2, [Week 2]

- Subjects will be clinically examined and given the study medications for next four weeks and also safety parameters will be assessed as per Table 1.
- Empty strips will be collected back by the investigators for compliance check.

## 3) Visit 3 [Week 6]

- Subjects will be clinically examined and given the study medications for next 6 weeks and also safety and efficacy parameters will be assessed as per Table 1.
- Empty strips will be collected back by the investigators for compliance check.

## 4) Visit 4 [Week 12]

- Subjects will be clinically examined and safety and efficacy parameters will be assessed as per Table 1.
- Empty strips will be collected back by the investigators for compliance check.

Unscheduled visits are allowed any time during the study for any untoward effect. Such visits will be recorded in the case record forms (CRFs).

If further investigations are required in case of any AE, investigator will assess the AE and take necessary action, if required. Subjects will be advised to contact the investigator for any complaints within the next two weeks.

During the above period, if any subject misses the drug administration up to 3 days, it will not be considered drop-out or protocol deviation.

During the 12 week program, a designated person from the centre will preferably interview the subject for his/her general health, telephonically.

|                                                         |                                                 |                                                           |
|---------------------------------------------------------|-------------------------------------------------|-----------------------------------------------------------|
| Prepared by:
[name]
Date: 22.06.2010 | Approved by:
[name]
Date:22.06.2010 | Protocol No. ZYH1.09.003.01 .PROT
Version No.: 1.0 (R) |
|---------------------------------------------------------|-------------------------------------------------|-----------------------------------------------------------|

|                                                                                  |                                                                                           |              |
|----------------------------------------------------------------------------------|-------------------------------------------------------------------------------------------|--------------|
| [figure not shown] | Clinical trial Protocol for ZYH1 – Phase II
ZYH1.09.003.01.PROT

DCGI Submission | Confidential |
|----------------------------------------------------------------------------------|-------------------------------------------------------------------------------------------|--------------|

**Table 1: Visit and Investigation Schedule**

| Activity                                                                                                                                                                                                             | Screening /
Enrolment
Visit 1
(Wk ≥-1 to 0) | Visit 2
(Week 2) | Visit 3
(Week 6) | Visit 4
(Week 12) |
|----------------------------------------------------------------------------------------------------------------------------------------------------------------------------------------------------------------------|------------------------------------------------------|---------------------|---------------------|----------------------|
| Demographics                                                                                                                                                                                                         | ✓                                                    |                     |                     |                      |
| Inclusion / Exclusion criteria                                                                                                                                                                                       | ✓                                                    |                     |                     |                      |
| Informed Consent                                                                                                                                                                                                     | ✓                                                    |                     |                     |                      |
| Medical History                                                                                                                                                                                                      | ✓                                                    | ✓                   | ✓                   | ✓                    |
| Vital Signs & Physical Examination                                                                                                                                                                                   | ✓                                                    | ✓                   | ✓                   | ✓                    |
| Efficacy studies:
Laboratory:
1. Triglyceride
2. LDL
3. VLDL
4. HDL
5. Total cholesterol
6. Non HDL Cholesterol
7. Apo(a)
8. Apo B
9. Fasting insulin and C-peptide for HOMA beta & IR | ✓                                                    |                     | ✓                   | ✓                    |
| Laboratory studies(safety)
1. CBC
2. LFT
3. RFT
4. CPK                                                                                                                                                   | ✓                                                    | ✓                   | ✓                   | ✓                    |
| ECG                                                                                                                                                                                                                  | ✓                                                    |                     |                     | ✓                    |
| Pregnancy test for female subjects (advise for contraception)                                                                                                                                                        | ✓                                                    |                     |                     |                      |
| Dispensing of Study Medication                                                                                                                                                                                       | ✓                                                    | ✓                   | ✓                   |                      |
| Study Medication Tablet Count                                                                                                                                                                                        |                                                      | ✓                   | ✓                   | ✓                    |
| Recording of Adverse Events                                                                                                                                                                                          |                                                      | ✓                   | ✓                   | ✓                    |
| Global Tolerability Assessments                                                                                                                                                                                      |                                                      |                     |                     | ✓                    |
| Study Completion                                                                                                                                                                                                     |                                                      |                     |                     | ✓                    |

|                                                         |                                                 |                                                           |
|---------------------------------------------------------|-------------------------------------------------|-----------------------------------------------------------|
| Prepared by:
[name]
Date: 22.06.2010 | Approved by:
[name]
Date:22.06.2010 | Protocol No. ZYH1.09.003.01 .PROT
Version No.: 1.0 (R) |
|---------------------------------------------------------|-------------------------------------------------|-----------------------------------------------------------|

|                                                                                  |                                                                                           |              |
|----------------------------------------------------------------------------------|-------------------------------------------------------------------------------------------|--------------|
| [figure not shown] | Clinical trial Protocol for ZYH1 – Phase II
ZYH1.09.003.01.PROT

DCGI Submission | Confidential |
|----------------------------------------------------------------------------------|-------------------------------------------------------------------------------------------|--------------|

### 6.3 ADHERENCE TO PROTOCOL

Investigator shall strictly adhere to the protocol and GCP guidelines.

All subjects will be strictly required to follow the instructions given to them as per this protocol. For any deviation or violation from protocol, considered serious by investigator, the subject may be withdrawn from the trial. [Section 3.4].

|                                                         |                                                 |                                                           |
|---------------------------------------------------------|-------------------------------------------------|-----------------------------------------------------------|
| Prepared by:
[name]
Date: 22.06.2010 | Approved by:
[name]
Date:22.06.2010 | Protocol No. ZYH1.09.003.01 .PROT
Version No.: 1.0 (R) |
|---------------------------------------------------------|-------------------------------------------------|-----------------------------------------------------------|

|                                                                                  |                                                                                           |              |
|----------------------------------------------------------------------------------|-------------------------------------------------------------------------------------------|--------------|
| [figure not shown] | Clinical trial Protocol for ZYH1 – Phase II
ZYH1.09.003.01.PROT

DCGI Submission | Confidential |
|----------------------------------------------------------------------------------|-------------------------------------------------------------------------------------------|--------------|

## 7. STATISTICS

### 7.1 POPULATION

#### 7.1.1 Efficacy population

##### 7.1.1.1 Intention-to-treat population (ITT):

The intention-to-treat (ITT) population will be the set of all subjects who receive study medication and have at least one post baseline efficacy data available.

##### 7.1.1.2 Per-protocol population (PP):

The per-protocol population (PP) will be the set of all subjects who receive study medication and complete Week 12 of the study in compliance to the protocol.

The PP analysis will be considered as definitive, while the ITT analysis will be considered as supportive during the trial analysis.

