### 3.4 WITHDRAWAL CRITERIA

The investigator may withdraw a subject from the study for any of the following:

- Subject who reports serious AEs (SAE)
- Subject who develops any serious/severe diseases which requires admission in intensive care unit (ICU) or interventional surgery, even if it is not related with investigational drugs
- Any subject found to have entered the study in violation of this protocol or if the subject is uncooperative during the study.
- Any subject who interrupts the study medication for longer than 4 consecutive days.

|                                                         |                                                 |                                                           |
|---------------------------------------------------------|-------------------------------------------------|-----------------------------------------------------------|
| Prepared by:
[name]
Date: 22.06.2010 | Approved by:
[name]
Date:22.06.2010 | Protocol No. ZYH1.09.003.01 .PROT
Version No.: 1.0 (R) |
|---------------------------------------------------------|-------------------------------------------------|-----------------------------------------------------------|

|                                                                                  |                                                                                           |              |
|----------------------------------------------------------------------------------|-------------------------------------------------------------------------------------------|--------------|
| [figure not shown] | Clinical trial Protocol for ZYH1 – Phase II
ZYH1.09.003.01.PROT

DCGI Submission | Confidential |
|----------------------------------------------------------------------------------|-------------------------------------------------------------------------------------------|--------------|

- If it is felt in Investigator's / Medical Expert's opinion that it is not in the subject's best interest to continue.
- In case a subject becomes pregnant, then she will be withdrawn from the trial.
- Subject who do not report to the clinic on +/- 4 days as per the visit schedule.
- Subject's lack of compliance to the study protocol
- Any subject who requires the use of an unacceptable concomitant medication.
- Any subject who wishes to withdraw his / her consent for participation in the study.

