### 7.2.2 Efficacy analysis

The primary efficacy variable is the reduction in Triglyceride (TG) at Week 6 and 12 of the treatment period compared with baseline. The change from baseline will be determined as the difference between the means for the treatment period (Weeks 6 and 12) and the baseline.

For the efficacy endpoints, treatment effect will be evaluated using an analysis of variance (ANOVA) model with factors for baseline and treatment. Treatment effects will be estimated using the least-square means and 95% confidence intervals (CIs) from the ANOVA model. Statistical significance will be defined as a two-sided p-value <0.05.

All other secondary endpoints would be analysed using appropriate statistical methods.

Intent-to-treat (ITT) and/or Per Protocol (PP) analysis will be carried out for the study trial. The PP analysis will be considered definitive while the ITT analysis will be considered supportive during the trial analysis. All the subjects enrolled in the study will be considered for the safety analysis.

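### The definitive efficacy result comes from compliant Week 12 completers only, which may bias the TG reduction, probably favourably, in a trial without a control arm

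*Protocol*

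**What the plan says.** Section 7.1.1.2 of the protocol limits the PP set to subjects who "receive study medication and complete Week 12 of the study in compliance to the protocol" and then ranks the analyses: "The PP analysis will be considered as definitive, while the ITT analysis will be considered as supportive during the trial analysis". The same ranking stands in section 7.2.2 and in the synopsis under Statistical methods.

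Section 7.1.1.1 defines the ITT set as "all subjects who receive study medication and have at least one post baseline efficacy data available". In Table 1 the first efficacy sample after baseline is at Week 6. Section 7.2.2 adds: "Intent-to-treat (ITT) and/or Per Protocol (PP) analysis will be carried out for the study trial".

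Section 6.1 describes the design as "A prospective, multi-centric, open-label, single arm study to evaluate the safety and efficacy of 4mg of ZYH1". The primary endpoint (sections 2.2 and 5.1.1) is percent change in TG from baseline to Week 6 and to Week 12.

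Section 3.4 lists reasons for which the investigator may withdraw a subject. They include an SAE, a dosing interruption, an unacceptable co-medication, non-compliance, and this one: "Subject who do not report to the clinic on +/- 4 days as per the visit schedule". Section 6.3 (Adherence to protocol) adds withdrawal for any deviation that the investigator regards as serious.

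**The concern.** Membership of the definitive set is settled after treatment starts. Stopping early, interrupting the drug, needing another medicine or withdrawing consent can each be related to how well a subject tolerates or responds to ZYH1. Several routes out are judgement calls by an investigator who knows the treatment. Section 4.2.1 also allows discretionary rescue for hypertriglyceridemia, which suggests that TG results can inform decisions during treatment.

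A randomised comparison may share some of this selection between arms. Here there is one arm, so all of it enters the estimate. The headline figure would describe compliant completers and could be read as the effect in everyone treated with ZYH1 4 mg.

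The supportive analysis is a weak safeguard. Read literally, it is optional, and it leaves out treated subjects with no efficacy value after baseline, in practice those lost before Week 6.

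**Working it through.** **1. What the protocol fixes.** The choice of PP is stated three times, so it is not a detail left to the SAP. Section 7.2.3 says only that the SAP will describe the analyses further.

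**2. Loss of Week 6 data.** Take a compliant subject with a valid Week 6 TG who stops at Week 8. The subject has not met the requirement to "complete Week 12 of the study in compliance to the protocol" and is outside PP. The Week 6 value, half of the primary endpoint, is lost from the definitive result. The ITT set keeps it.

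**3. Is PP membership determinate?**
- Rescue: section 4.2.1 allows rescue at discretion and withdraws the subject only if the medicine violates the protocol. Section 4.2.2 bars other lipid-lowering drugs. The two sections conflict, so the PP status of a rescued subject is undetermined.
- Dosing gaps: the synopsis makes a gap of more than 3 consecutive days a serious deviation. Section 3.4 makes a gap of more than 4 consecutive days a reason for withdrawal. The PP status of a subject between the two limits is unclear.

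**4. Size of the bias.** The protocol states no expected effect, SD or dropout rate. Section 3.1 gives only 50 subjects, 80% power and the 5% level, so there is no plan figure to reproduce. With f the excluded share:

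all-treated mean = (1 - f) x retained mean + f x excluded mean

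PP mean - all-treated mean = f x (retained mean - excluded mean)

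Assumptions, none of them in the protocol: retained mean -25%; f = 10%, 20% or 30%; excluded mean 0%, -12.5%, -25% or -35%. A negative bias makes PP look too favourable.

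| Excluded mean | f = 10%: all-treated (bias) | f = 20%: all-treated (bias) | f = 30%: all-treated (bias) |
|---|---|---|---|
| 0% | -22.5% (-2.5) | -20% (-5) | -17.5% (-7.5) |
| -12.5% | -23.75% (-1.25) | -22.5% (-2.5) | -21.25% (-3.75) |
| -25% | -25% (0) | -25% (0) | -25% (0) |
| -35% | -26% (+1) | -27% (+2) | -28% (+3) |

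For example, with f = 20% and no change in excluded subjects: 0.8 x (-25%) + 0.2 x 0% = -20%, and the bias is 0.2 x (-25 - 0) = -5 points.

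The bias scales with the assumed effect. With -40% in retained subjects and none in excluded subjects it is 4, 8 or 12 points. The sign depends wholly on how excluded subjects respond.

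**The case against.** The ranking of the analyses is prespecified and open, the study is an exploratory Phase II trial, and a PP result would be labelled as such. Section 7.1.1.2 gives both analyses a role, so the and/or wording may be loose drafting. These points are fair, but they do not remove the selection from the result that the protocol calls definitive.

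Three stronger readings are tempting, and the protocol does not support them.

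- **Subjects with SAEs or rescue are removed by rule.** Section 3.4 says only that the investigator may withdraw a subject. The synopsis withdrawal list does not name SAEs, and a subject with an SAE who completes and complies stays in PP. Late visits and interruptions are serious deviations in the synopsis, so exclusion from PP is plausible, but withdrawal is again discretionary. The status of rescued subjects is undetermined.
- **The TG reduction is overstated.** The protocol holds no data on response by completion status, and a late visit has no evident link to TG. Rescue may itself lower TG, so adding rescued subjects back need not shrink the effect. A favourable bias is probable, not shown.
- **PP loses power against the treated set.** Back-solving 80% power at n = 50 (two-sided one-sample t) gives a standardised change of 0.404. At that value 45, 40 or 35 subjects give 75.5%, 70.3% or 64.2%. This holds the effect fixed. If excluded subjects do not change, they dilute the all-treated effect: with a mean of -25% and SD 25/0.404 = 61.9 within each group, all 50 give about 71%, 60% or 49%, less than PP. Section 3.1 also does not say whether 50 means enrolled or evaluable. Power is no argument for the change.

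**Conclusion.** The concern holds as a risk of bias built into the definitive analysis. In this uncontrolled, open-label trial the headline TG result rests on a set chosen by events after baseline, partly at the investigator's discretion, with membership rules that are not determinate. It also discards valid Week 6 primary-endpoint data.

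The direction is probably favourable to ZYH1. Under the assumed -25% in retained subjects and 10% to 30% excluded, the bias is 2.5 to 7.5 points if excluded subjects do not change. It is zero if they respond equally and reverses if they respond better. These figures illustrate the identity and are not estimates from the protocol. Because the choice determines the trial's main efficacy claim, it should be changed before the data are analysed.

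**What to change.** - Make the definitive set all subjects who receive at least one dose and have a baseline TG. Analyse all observed Week 6 and Week 12 TG values in a repeated-measures model. This model is a proposal; section 7.2.2 names an ANOVA.
- Make PP supportive, and replace and/or by and, so that both analyses are always reported.
- Where the subject agrees, take the Week 12 fasting TG also after early stopping or outside the visit window.
- Prespecify how TG values after rescue enter the analysis. Without such a rule, using all observed values could make the estimate look more favourable.
- Add a sensitivity analysis with missing Week 12 TG set to the baseline value. This also brings in subjects who have no value after baseline.
- Reconcile sections 4.2.1 and 4.2.2 on rescue, and the synopsis and section 3.4 on dosing gaps, so that PP membership is determinate.

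The cost is protocol and SAP wording and a few extra blood samples. The headline estimate may be somewhat less favourable.
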